### Secondary outcomes

The secondary outcomes will consist of: a) body composition assessed every 3 months using a bioelectrical impedance analyzer (patients with 12-h fasting); b) resting metabolic rate evaluated by indirect calorimetry at baseline and 6 months later (patients with 12-h fasting); c) satiety evaluated twice (at baseline and 6 months later) by VAS and answered 2 h after three main meals (breakfast, lunch, and dinner); d) kidney function assessed by serum creatinine through estimated glomerular filtration rate (MDRD formula) and 24-h urine test with albumin and protein (every 3 months); e) glycated hemoglobin evaluated every 3 months; f) lipid profile evaluated every 3 months by total cholesterol, HDL cholesterol, and triglycerides (with 12-h fasting) laboratory tests; and g) inflammation assessed through high-sensitivity C-reactive protein at baseline and 6 months later.

### Statistical analyses

Continuous variables with normal distribution will be expressed as mean ± standard deviation. The Shapiro-Wilk test will be used for normality assessment; asymmetrically distributed continuous variables will be expressed as median and interquartile range; and categorical variables will be expressed as absolute and relative frequencies. For between-group comparisons, the Student’s *t* test will be used for normally distributed variables, and the Mann–Whitney *U* test for asymmetrically distributed variables. A paired *t* test will be used for within-group analysis of body weight and body composition. The Chi-square or Fisher’s exact tests will be used to evaluate associations between categorical variables. The generalized estimating equations test with Bonferroni adjustment will be used for comparison between variables during the study period. The significance level will be set lower than 5%, and all data will be analyzed in SPSS 20.0 (SPSS Inc., Chicago, IL, USA).

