### Sample size

Sample size calculations were carried out in WINPEPI 11.20 (Brixton Health, Israel) based on data from Souza et al. [31]. To find a difference of 5% in body weight between groups 1 year after the transplant, considering a standard deviation of 8.8%, a significance level of α ≤ 0.05 and a statistical power of 80%, the minimum sample size will be 98 patients. Because of possible dropouts, we will include 120 patients (60 randomized to each group).

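### Continuous outcomes are to be compared by unadjusted t or Mann-Whitney tests chosen by a normality check; a prespecified baseline-adjusted model would be more precise for the secondary outcomes and would fix what is compared

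*Protocol article*

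**What the plan says.** The protocol's Statistical analyses section sets the between-group rule for continuous variables: the Student's t "test will be used for normally distributed variables", and the Mann-Whitney U test is used for asymmetric ones. The choice rests on a pretest: "The Shapiro-Wilk test will be used for normality assessment". No covariate is named.

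The same section also lists:
- paired t tests within each group for body weight and body composition;
- Chi-square or Fisher's exact tests for categorical variables;
- a GEE analysis over the study period with Bonferroni adjustment. Its model terms are not given, and it is not tied to any endpoint.

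Baselines are collected. Study protocol has weight and waist measured at all nine visits. Secondary outcomes has "resting metabolic rate evaluated by indirect calorimetry at baseline and 6 months later", and the same two time points for satiety and C-reactive protein (CRP). Body composition, kidney function, glycated hemoglobin and lipids are measured every 3 months. I read those series as starting at baseline.

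The primary outcome is a threshold: whether weight gain stays under 5%, at 12 months according to the Abstract.

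**The concern.** A patient's baseline value usually predicts the follow-up value of the same measurement. A between-group test that leaves it out has a larger standard error than necessary. Resting metabolic rate, satiety and CRP have one baseline and one later measurement, which is the standard setting for ANCOVA. The only listed test that plainly uses baseline is the paired t test, and a within-group test does not estimate the effect of the diet.

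The pretest raises a separate issue. If Shapiro-Wilk decides between t and Mann-Whitney, the observed data decide whether means or ranks are compared. Two outcomes, or two visits of one outcome, may then be reported on different quantities, and Mann-Whitney by itself gives no mean difference.

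At stake are the width of the intervals for the secondary outcomes, including kidney function, which the Discussion treats as the open safety question, and an analysis that is fixed before the data are seen.

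**Working it through.** **1. The plan's own figure.** Inputs from Sample size: "To find a difference of 5% in body weight between groups 1 year after the transplant", "considering a standard deviation of 8.8" (per cent), "a significance level of α ≤ 0.05 and a statistical power of 80" (per cent). Sidedness is not stated; I take two-sided.

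n per arm = 2 × [8.8 × (1.960 + 0.842) / 5]² = 48.6, rounded up to 49, so 98 in total. This matches "the minimum sample size will be 98 patients". (One-sided would give 78.) The trial was therefore sized as an unadjusted two-sample comparison on a percentage scale. Power at 49 per arm is 80.3% by the normal approximation.

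**2. Variance of the treatment effect.** Let ρ be the correlation between baseline and follow-up, with equal variances at both times. Relative to a t test on follow-up values:
- ANCOVA: 1 − ρ²
- change score: 2(1 − ρ)
- ANCOVA relative to change score: (1 − ρ²) / [2(1 − ρ)] = (1 + ρ)/2

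The protocol gives no ρ, so the range is assumed.

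| ρ (assumed) | ANCOVA / follow-up t test | ANCOVA / change score |
|---|---|---|
| 0.5 | 0.75 | 0.75 |
| 0.7 | 0.51 | 0.85 |
| 0.8 | 0.36 | 0.90 |
| 0.9 | 0.19 | 0.95 |

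The middle column applies if the t tests use follow-up values. The last column applies if they use changes. It also applies if the GEE treats baseline as an ordinary visit, because with two visits its arm-by-visit contrast is a difference in change. The protocol does not say which of these is meant.

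**3. Percent weight change.** Baseline weight is already in the denominator. Here the relevant correlation is between baseline weight and percent change, assumed 0 to 0.3.

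| Correlation (assumed) | Variance ratio | Total N for 80% power | Power at 49 per arm |
|---|---|---|---|
| 0 | 1.00 | 98 | 80.3% |
| 0.1 | 0.99 | 98 | 80.7% |
| 0.2 | 0.96 | 94 | 81.9% |
| 0.3 | 0.91 | 90 | 83.8% |

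For example, at 0.3: 48.6 × 0.91 = 44.2, rounded up to 45 per arm, 90 in total.

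**4. The normality switch.** Simulation with 49 per arm and 5,000 replicates per scenario. Mann-Whitney was used if Shapiro-Wilk had p < 0.05 in either arm, and t otherwise. Applying the check by arm is an assumption. The alternative is a shift of 5 with SD 8.8.

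| Data | Switched to Mann-Whitney (null) | Type I error, two-stage | Power: t / Mann-Whitney / two-stage |
|---|---|---|---|
| Normal | 10.2% | 5.2% | 79.4% / 77.4% / 79.1% |
| Lognormal (log SD 0.5) | 99.2% | 5.0% | 79.6% / 91.9% / 91.9% |
| t, 5 df | 58.6% | 5.2% | 79.1% / 86.0% / 85.4% |

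The simulation error of a 5% rate is √(0.05 × 0.95 / 5000) = 0.3 percentage points, so type I error shows no inflation. With exactly normal data, about one trial in ten still changes from means to ranks by chance. With skewed data ranks do better than raw means, so the switch should be replaced by a scale fixed in advance and not by a t test on raw values.

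**The case against.** **The GEE may already use baseline.** Baseline is one of the scheduled time points, and a GEE with arm and visit can include it. An article may leave model terms to a fuller document. This stands so far as one cannot say that the plan throws baseline values away. It does not remove the point: the t/Mann-Whitney rule is stated alongside the GEE, neither is given priority, and a GEE with baseline as an ordinary visit still leaves the (1 + ρ)/2 gain unused for two-visit outcomes.

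**A reader might infer that the main result loses much of its precision.** The documents do not support this. The primary outcome is binary and falls under Chi-square or Fisher, so neither the t test nor the pretest touches it. Percent weight change already contains baseline weight, and step 3 shows a small gain. A large loss for weight would arise only if raw kilograms at 12 months were compared: with an assumed baseline mean of 70 kg and SD of 10 to 16 kg, power would be 29% to 16%, against about 79% with ANCOVA. Nothing in the protocol says that this is planned, and the percentage scale of the sample size points the other way.

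**A reader might also infer bias from chance imbalance.** With "we will include 120 patients (60 randomized to each group"), the standardised baseline difference has SD √(2/60) = 0.183, and a given covariate differs by more than 0.2 SD with probability about 27%. That is true of any unstratified trial of this size. The unadjusted test remains unbiased over randomisation and keeps its type I error. Adjustment improves efficiency; it does not repair validity.

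**Mann-Whitney need not leave the reader without an estimate.** Medians and interquartile ranges are to be reported for skewed variables, and a Hodges-Lehmann shift could be added. This is fair. What remains is that the quantity compared is not fixed beforehand.

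**Conclusion.** The point holds for continuous outcomes, and in practice mainly for the secondary ones: body composition, resting metabolic rate, satiety, eGFR, glycated hemoglobin, lipids and CRP. For ρ of 0.5 to 0.9, adjusting for baseline would reduce the variance by 25% to 81% if follow-up values are otherwise compared, and by 25% to 5% if changes are. These figures rest on assumed correlations and on equal variances at the two times. For percent weight change the saving is about 0–9%, and the primary outcome is not affected.

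The normality switch is a matter of prespecification. It shows no type I error inflation in the cases simulated, but it leaves the choice between means and ranks to the data. Nothing here invalidates the trial; this is an inexpensive improvement that should be made.

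**What to change.** In Statistical analyses, replace the between-group rule for continuous efficacy outcomes with the following:

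- **One follow-up measurement** (resting metabolic rate, satiety, CRP): a linear model with arm and the outcome's own baseline value. Report the adjusted difference with its confidence interval.
- **Several follow-up visits:** the planned GEE with arm, visit, arm-by-visit and the baseline value as covariate, named as the between-group analysis in place of separate tests at each visit.
- **Percent weight change**, where analysed: the same, with baseline weight as covariate.
- **Skewed variables** (CRP, triglycerides, albuminuria): log scale fixed in advance, with a stated rule for zero or below-detection values.
- **Shapiro-Wilk, t and Mann-Whitney:** description only.

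The Chi-square or Fisher analysis of the primary outcome needs no change on this account.

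Cost: no further patients, visits or measurements, and a GEE in SPSS is already planned. Because the trial is open-label and, according to Trial status, 60 patients have started, the change must be a dated and justified amendment, made before any comparison of outcomes by arm.

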## Discussion

To the best of our knowledge, this is the first randomized clinical trial that will evaluate the impact of a high protein and low GI diet on weight maintenance or weight gain lower than 5% of body weight after kidney transplantation. Furthermore, this study will evaluate other relevant parameters related to metabolic outcomes since we hypothesized that this dietetic intervention may be able to improve body composition, resting metabolic rate, satiety, inflammation, and lipid and glycemic profiles.

Importantly, there is still concern related to a high protein intake and kidney damage based on some previous studies that showed an association between a high protein intake and worsening of renal function [37–40]. However, data on the impact of protein intake on long-term outcome in kidney transplant recipients are scarce [40–43]. Bernardi et al. evaluated a low-protein, low-lipid, and low-sodium diet in a 12-year follow-up study and showed a protective effect for the kidney with this diet [40], but the interpretation of the results are limited and controversial. Van Den Berg et al. [41] studied the association between protein intake and blood pressure, proteinuria, and creatinine clearance in a cross-sectional study with 625 renal transplant recipients, and no deleterious effects of the diet were identified. Interestingly, in a cohort of 940 kidney transplant recipients, a higher protein intake was associated with protection against mortality and graft failure [42]. These results were confirmed in a more recent cohort of 604 kidney transplant recipients with 7 years of follow-up [43]. Said et al. have shown that a high protein intake was associated with improvements in muscle mass and with reduced risk of mortality and graft failure [43], suggesting that a relatively high protein intake may be beneficial to kidney transplant recipients.

Other studies evaluating the impact of dietary interventions in kidney transplant recipients show conflicting results, mainly limited by the study design [12–14]. Thus, due to lack of high-quality evidence data on this issue, there are no guidelines or recommendations for a specific nutritional intervention to manage weight gain and obesity after kidney transplantation [44–46].

Since it is not possible to blind participants and researchers involved in this study, there are possible risks of bias. In order to diminish these risks, we will be evaluating standard measurements of weight and other anthropometric and laboratory tests. Furthermore, to reduce the potential for confounding due to measurement variability, a single investigator will perform all the measurements using the same instruments throughout the study and the same dietitian will perform the nutrition intervention protocol.

### Trial status

The trial is ongoing. Sixty patients have started the study protocol and additional patients are being recruited.

## Abbreviations

BMI: Body mass index
FAO: Food and Agriculture Organization
GI: Glycemic index
MDRD: Modification of diet of renal disease
SPIRIT: Standard Protocol Items: Recommendations for Interventional Trials
USDA: United States Department of Agriculture
VAS: Visual analogue scale
